### Self-reported physical functioning and quality of life

The physical functioning subscale of the short form 36 (SF-36), version 2 is used as a measure of physical functioning in the present study. Besides subjective measures of physical functioning, objective assessments are also included in the study as described below.

Furthermore, Quality of life is measured by the SF-36, the Kidney Disease Quality of Life Instrument - Short Form (KDQOL-SF) and the EuroQol (EQ-5D). SF-36 consists of 36 items which measure self-reported physical functioning, social functioning, role limitations due to physical and emotional problems, mental health, vitality, pain and general health on a scale of 0–100. The scores are added up into two summary scores, the physical component summary (PCS) and the mental component summary (MCS). The KDQOL-SF contains 13 items targeted at quality of life related to matters of special relevance for renal patients, such as disease burden and social interaction [38]. The KDQOL-SF has been translated into Dutch and validated in Dutch patient population [39]. The EQ-5D is a general questionnaire and contains questions on mobility, self-care, usual activities, pain/discomfort and anxiety/depression and a VAS scale for self-rated health.

### Objective measures of physical functioning

#### Muscle strength

Maximal muscle strength is assessed for multiple muscle groups (Additional file 1: Table S1). Maximal muscle strength of knee extensors, knee flexors, back and chest muscles are included as an outcome measure. Maximal muscle strength is determined using the one-repetition maximum (1RM) method under supervision of a qualified physiotherapist. The 1RM refers to the resistance at which the participant is only just able to perform the exercise correctly. For each strength test, the physiotherapist estimates the 1RM of the subject for the particular exercise machine. The increments are chosen in such a way that the participant reaches 1RM after 3–5 one-repetition sets.

#### Aerobic capacity

Aerobic capacity is determined by symptom-limited graded cycle ergometry, which is commonly used in renal transplant patients and considered the gold standard for determining aerobic capacity [1]. The test determines the maximal workload (Wpeak) and maximal oxygen uptake (VO_2_peak) using a respiratory gas analyzer (Cortex Metalyzer 3B breath analyser, Cortex Biophysik GmbH, Leipzig, Germany). VO_2_peak indicates the peak amount of oxygen that the body is able to utilize during sustained physical exertion [1]. The cycle ergometers used for all participants is a Lode Corival 906900 (Lode B.V., Groningen, Netherlands). After a period of rest and 1 min pedaling without workload, the bicycle workload is increased gradually every minute by 10 to 25 W depending on the participants’ expected exercise capacity. The incremental increase in workload is done in such a way that maximal exercise capacity is reached within 8–12 min after starting the exercise test. The workload during the test is blinded for the participant. Participants cycle at a cadence of 60–70 rotations per minute until exhaustion. The maximal cycle ergometry tests are medically supervised by a sports physician. Before and during the test, the participant’s heart function is monitored using ECG-monitoring. In addition, heart rate, blood pressure and oxygen saturation are monitored. The test is stopped when ECG abnormalities occur, systolic blood pressure rises over 250 mmHg or diastolic blood pressure rises over 120 mmHg, or if blood pressure falls with more than 20 mmHg.

The sub-maximal exercise test is performed on a general fitness cycle-ergometer under supervision of a qualified physiotherapist. It consists of a 2 min warm-up, 10 min cycling at 50% Wpeak, followed by 70% of Wpeak at 60–70 rpm until exhaustion, but for a maximum of 20 min. A longer test duration indicates better exercise capacity. Heart rate and blood pressure are monitored during the submaximal cycle ergometry using an Omron M6 (Omron, Tokyo, Japan).

#### Balance and mobility

The Short Physical Performance Battery (SPPB) is used to determine lower extremity function as a measure for balance and mobility. SPPB is a common and reliable standardized measure of balance, gait speed, and chair stand tests used to measure physical performance [40, 41].

For daily physical activity, the Baecke questionnaire is used to assess habitual PA with questions on PA in different domains such as school/work, sports practice and leisure-time physical activity [42]. Responses are combined producing an overall habitual activity score. This has been validated against the doubly-labeled water method, showing a strong correlation (*r* = 0.69, p = <0.001) [43]. A validated spring-levered step counter (Yamax Digiwalker SW-200, Lees Summit, Missouri (YX200)) is used to objectively measure daily steps as an objective measure of physical activity level. Participants are instructed to wear the step counter for 5 days, and record the date, number of steps at each of the five days, as well as the time in minutes spent on cycling, swimming and fitness on each of those 5 days.

### Body composition and nutrition status

Body composition is estimated using a multi-frequency bio-electrical impedance device (BIA, Biostat Quadscan 4000, Douglas, Isle of Man) at 5, 50, 100 and 200 Hz, which allows for distinction between body fat mass and lean body mass taking into account differences in volume status. BIA is used to estimated fat mass, fat free mass and body fat percentage. Muscle mass is estimated as fat free mass from BIA and from 24-h urinary creatinine excretion. The 24-h creatinine excretion is considered a reliable measure of muscle mass even in patients with advanced renal failure, in elderly people, and in patients with wasting conditions [3, 44]. Anthropometry measures include bodyweight, height, waist- and hip circumference. All anthropometry measures are done twice. Bodyweight is measured in lightweight clothing without shoes, preferably in the morning, on a calibrated scale (Seca 877, Seca GMBH, Hamburg, Germany), to the nearest 0.1 kg. Height is measured using a wall-secured stadiometer (Seca 222, Seca GMBH, Hamburg, Germany). Waist circumference is measured with the subject in standing position at the level midway between the lowest rib and iliac crest at the end of an expiration to the nearest 0.1 cm. Waist circumference is also measured in participants with polycystic kidney disease which may create noise in the data, although in case a participant had polycystic kidney disease this is clearly defined in our dataset. Hip circumference is measured as the maximum circumference over the trochanter major to the nearest 0.1 cm. A tape with standardized retraction mechanism (Seca 201, Seca GMBH, Hamburg, Germany) is used. Nutrition status is assessed by subjective global assessment (SGA) [45]. The SGA consists of an anamnesis (questions about change in bodyweight, food intake and gastrointestinal symptoms) and a physical examination (subcutaneous fat, muscular atrophy of the upper and lower body) resulting in an SGA-classification (seriously malnourished, moderately malnourished or normally nourished).

### Cardiometabolic risk factors

Blood samples are collected after an overnight fast and assayed for triglycerides, total cholesterol, HDL- and LDL cholesterol for lipid profile and for glucose and insulin to calculate insulin resistance (HOMA2-index) [46]. Impaired glucose metabolism is measured using 7-timepoint Oral Glucose Tolerance Test [47]. After fasting blood sampling, the participant consumes a 300 ml glucose solution which contains 75 g of glucose (82.5 g glucose monohydrate). After glucose ingestion, blood is drawn at 10, 20, 30, 40, 60, 90 and 120 min. During the test participants are not allowed to eat or drink, except for a limited amount of water. Blood samples are stored until further analysis. Oral Glucose Tolerance Testing was performed in a subsample (participants from University Medical Center Groningen).

### Renal parameters

Serum creatinine concentrations are determined using the Jaffé method. Creatinine clearance is calculated from 24-h urinary creatinine excretion and serum creatinine. Medical information is collected from the participants’ medical files, including renal parameters (underlying cause of the renal disease, dialysis duration and type, transplantation type, time since transplantation), medication use, hospital admissions, complications after transplantation, co-morbidities and mortality. Medication is derived from the participants’ medical records.

### Questionnaires

A quite extensive set of questionnaires to address potential psychological aspects, mostly aspects of motivation, is included in the questionnaires for participants. Details about moment of assessment is given in Table 1. The following questionnaires are included: Basic Needs Satisfaction in General Scale [48, 49]Basic Psychological Needs in Exercise Scale [50], Behavioral Regulation in Exercise Questionnaire version 2 [51], Treatment Self-regulation Questionnaire [52], Intrinsic Motivation Inventory [53], Exercise Motivations Inventory version 2 [54], Perceived Competence Scale [55, 56] and the Health Care Climate Questionnaire [55, 57]. Furthermore, fear of movement is determined using the 17-item Tampa Score for Kinesiophobia [58]. Questions are answered on a 4-point likert-type scale ranging from 0 (not true for me) to 4 (very true for me). Coping style is measured using the Utrecht Coping List, a Dutch 47-item questionnaire [59]. Coping style refers to a persons’ specific efforts to master, tolerate, or reduce stress in stressful conditions. Nutrition knowledge is estimated using items from a national survey, developed by the Netherlands Nutrition Center to assess knowledge of the Dutch dietary guidelines on dietary fibre, fruits, vegetables, calories, fats, and extended with items about potassium and sodium. Chronic fatigue is measured using the Dutch Checklist Individual Resilience (CIS-20) [60–62] consisting of 20 items covering the subjective experience of fatigue, reduction in motivation, reduction in concentration and reduction in physical activity. CIS-20 is tested thoroughly in the clinical setting among patients with chronic fatigue syndrome and other chronic diseases and healthy controls [63–65]. Work-induced fatigue is assessed by the Need for Recovery scale [66]. This 11-item questionnaire measures fatigue as a result of exposure to physical and mental demands imposed by work [66, 67]. Work participation is assessed using a previously developed questionnaire for patients with renal disease [68]. Furthermore, the ACT questionnaire contains questions about demographics, smoking, and alcohol consumption.

### Dietary intake

A three-day food diary is kept for two weekdays and one weekend day. Participants are instructed to fill out the food diary accurately using standard supply units or, in case of deviations, to weigh their food to improve estimate of consumption. Food diaries are analyzed by a dietitian, and the nutrition values are calculated using the software program EvryDietist, 6.4.2.1 (Evry, Alphen aan den Rijn, Netherlands), using the Dutch Food Composition Database 2016 to calculate macro- and micronutrient intake. As part of usual care all participants are instructed to collect a 24-h urine sample according to a strict protocol at the day before their visit to the outpatient clinic, from which dietary sodium intake is calculated. Twenty-four-hour urine collections are stored until further analysis.

### Process evaluation

Qualitative findings regarding organizing and carrying out the intervention is derived from focus groups with the participants, and separately with 1 focus group with professionals (physiotherapists, dieticians and lifestyle coaches). All participants that are randomized into the intervention groups are invited to take part in the focus group after they have finished the intervention. Each participant focus group lasts 90 min, during which they are asked a series of open questions to evaluate the exercise training phase, the follow-up phase, the lifestyle counseling sessions and dietary counseling sessions. The focus groups are recorded and the recordings are transcribed for analysis. A focus group with the professionals will be done at the end of the ACT study.

### Health economic analysis

Costs en cost effectiveness of the interventions will be studied from a societal perspective over a 15 month time horizon. The effectiveness of the interventions will be assessed using information about the health-related quality of life of the participants, measured using the EQ-5D [69]. This instrument measures health-related quality of life and 60 translates responses into a utility score. The EQ-5D measures health in five dimensions of health-related quality of life (mobility, self-care, usual activities, pain/discomfort, and anxiety/depression). Dutch-specific value sets will be used to translate responses into a utility score. Utility scores will be used to calculate quality-adjusted life-years (QALYs).

Healthcare consumption is measured using a standardized Dutch questionnaire. This questionnaire measures the amount of visits to a healthcare provider, and the means of travelling (i.e. walking/cycling, car, public transport, taxi or other). Unit costs from routinely available sources will be applied to the number of visits to calculate the total costs of these visits for each participant. The Dutch manual for cost-effectiveness analysis is used as a guideline for weighing the cost items [70, 71]. Additional cost calculations will be done for the interventions including personnel, materials, volume and overhead costs. The total costs and QALYs in the intervention groups will be compared to the total costs and QALYs in the control group. An incremental cost-effectiveness ratio (ICER) will be calculated to compare the exercise intervention, and the exercise + diet intervention with usual care. Furthermore, two cost-utility analyses will be done with EQ-5D as an outcome measure.

### Statistical analyses

Short term differences between groups will be tested using students T-test or linear regression, and long term differences will be tested using General Linear Mixed models. Time will be analyzed for exercise intervention (phase 1) and maintenance period (phase 2). Centers will be taken into account as random factor. Intention to treat principle will be applied in primary analyses. Per protocol analysis will be based on completion of the exercise training sessions, and attendance of dietary counseling sessions. Stratified analysis are foreseen for time after transplantation, socio-economic status and immunosuppressive regime. Furthermore, potential preset determinants of intervention outcome will be evaluated in a GLM model: gender, age, coping style, fear of movement, work participation and clinical factors.

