### Eligibility criteria

The target population for the study are adult RTR, recruited during routine post-transplantation care shortly, but at least within the first year after transplantation. Inclusion criteria are: written informed consent; age > 18 years; < 1 year after transplantation; approval for participation based on a general medical evaluation by their nephrologist. Exclusion criteria included the following: multiple organ transplantation; psychopathology or serious cognitive impairment; physical or clinical limitations that make participation impossible; pregnancy, negative screening verdict by the nephrologist or cardiologist. Participants receive a small financial reimbursement (10 Euro) for participation in the final follow-up measurement at 15 months. Participation in the exercise training sessions and dietary care are financed by research funds, and participants’ travel expenses are reimbursed. Pre-defined reasons to discontinue participation in the study included pregnancy and conversion to dialysis. Furthermore, reasons to discontinue participation are: changes in ECG during maximal aerobic capacity testing, systolic blood pressure > 250 mmHg, diastolic blood pressure > 120 mmHg or blood pressure decline of > 20 mmHg during maximal aerobic capacity testing, and severe cardio-pulmonary complaints during the exercise trainings sessions.

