### Screening, recruitment and randomization

All RTR patients are screened for eligibility during the post-transplantation recovery period, so within 7–10 days after surgery, by the nephrologist. Eligible RTR are invited to participate, informed about the study protocol and if agreed are asked to participate and sign written informed consent. In case of non-Dutch or non-English speaking patients, interpreters are used.

In total, 219 participants (73 per group) will be recruited. The sample size is based on the expected improvement on the physical functioning scale of quality of life of 13.8 points in the intervention group and 8.8 points in usual care (α=0.05, β= 0.80, SD = 11.0) [26]. A difference of 5.0 points between the standard effect is considered a relevant effect. This results in a required number of 57 RTR per group. Taking into account a potential dropout rate of 15% and a correction for heterogeneity between centers of 10%, this results in a total required number of 73 RTR per group (*N* = 219 in total). Randomization to one of the three arms is computerized using the ‘PROC SURVEYSELECT’ function in the software program SAS (Cary, North Carolina, USA). It is performed by an independent data management company hosting the data entry facility, who are not involved in conducting the study itself (Nefrovisie foundation, Utrecht, the Netherlands). Participants are randomized by block randomization in groups of 6–9 for rehabilitation centers and in groups of 3 for physiotherapy practices.

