### Outcomes

The primary outcome is the subdomain physical functioning of quality of life of the SF-36. Secondary outcomes include other evaluations of quality of life (SF-36, KDQOL-SF, EQ-5D), muscle strength (Additional file 1: Table S1), aerobic capacity, physical activity, gain in adiposity (body fat percentage by bio-electrical impedance assessment, BMI, waist circumference), and cardiometabolic risk factors (blood pressure, lipids, glucose metabolism). Furthermore, data on renal function, medical history, medication, psychosocial factors (motivation, kinesiophobia, coping style), nutrition knowledge, nutrition intake, nutrition status, fatigue, work participation, process evaluation and cost-effectiveness are collected. Effectiveness of the diet intervention will be determined at 15 months. To study barriers and success factors regarding lifestyle counseling in RTR, data are gathered on psychological factors including motivation, kinesiophobia, and coping style. A comprehensive overview of the measurements in the ACT trial is shown in Table 1.

**Table 1 Tab1:** Overview of measurements in the ACT trial

Outcome	Method	Time points
Quality of life		T0, T3, T6, T15
Physical functioning	SF-36 PF subscale [72, 73]	
Other subdomains and total	SF-36 [72, 73]	
Renal specific	KDQOL-SF [39]	
General	EQ-5D [69]	
Physical function		
Aerobic capacity	VO_2_peak ergometer test [74]	T0, T3, T6, T15
	Sub-maximal ergometer test	T0, T3, T6, T15
Muscle strength	1RM tests for leg extension, leg curl, chest press, close-grip pull-down	T0, T3, T6, T15
Balance and mobility	Short Physical Performance Battery [41]	T0, T15
Physical activity level	Baecke questionnaire [42]	T0, T3, T6, T15
	Step counter (Yamax SW200) [75]	T0, T3, T6, T15
Body composition		
Weight, Height, WC, HC	WHO guidelines [76]	T0, T3, T6, T15
Nutritional status (undernutrition)	SGA [77]	T0, T15
Body fat percentage	BIA (Biostat Quadscan 4000, Douglas, Isle of Man)	T0, T3, T6, T15
Muscle mass	BIA (Biostat Quadscan 4000, Douglas, Isle of Man)	T0, T3, T6, T15
	24-h creatine excretion [44, 78]	T0, T3, T6, T15
Cardiometabolic risk factors		
Blood pressure	(Speidel & Keller Maxi Stabil 3)	T0, T3, T6, T15
Blood lipids	TG, TC, HDL-C, LDL-C in fasting serum levels (Cholesterol oxidase-phenol aminophenazone method, MEGA AU 510; Merck Diagnostica, Darmstadt, Germany)	T0, T3, T6, T15
Glucose metabolism		
Insulin resistance	HOMA-IR (fasting glucose, insulin)	T0, T3, T15 (all)

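### The t-test option for short-term differences in SF-36 PF cannot carry the stated centre factor and is less efficient than adjusting for the T0 score

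*Protocol article*

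**What the plan says.** In the protocol article, Statistical analyses gives two methods for the short term, "Short term differences between groups will be tested using students T-test or linear regression", and another for later visits: "long term differences will be tested using General Linear Mixed models". It then adds: "Centers will be taken into account as random factor". Time is divided into the exercise phase and the maintenance phase. Supervised training lasts 3 months, so T3 is the natural reading of short term.

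The Outcomes section states: "The primary outcome is the subdomain physical functioning of quality of life of the SF-36". Table 1 there schedules this scale at T0, T3, T6 and T15, so a baseline value is collected. No separate method is given for the primary outcome, and the general sentence therefore governs it.

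Under Screening, recruitment and randomization, the sample size rests on an "expected improvement on the physical functioning scale of quality of life of 13.8 points in the intervention group and 8.8 points in usual care", with SD 11.0. The article does not say whether 11.0 is the SD of a score or of a change.

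**The concern.** Of the two short-term methods, only regression can be extended to hold a baseline covariate and centre. The t-test can hold neither, so it conflicts with the statement on centres in the same paragraph. The design also pays for centre differences, with a 10% addition to the sample size for heterogeneity between centres.

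The other cost is precision. The T0 score is planned for all participants, and adjusting for it narrows the confidence interval with no further recruitment. That matters here because a two-sided t-test on the article's own inputs falls short of the intended 80% power at the stated group size.

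**Working it through.** **Inputs from the article.** Difference 5.0 (13.8 minus 8.8), SD 11.0, alpha 0.05, power 0.80 (printed as beta), 57 per group before inflation, 15% dropout, 10% for centres, 73 per group recruited.

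**Assumed.** Two-sided test; one intervention arm against usual care with no multiplicity correction; baseline-follow-up correlation r from 0.4 to 0.7; equal SD at baseline and follow-up, needed only for the change-score formula.

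**The article's own figure.** n = 2 × [11.0 × (1.96 + 0.84) / 5.0]² gives 76 per group two-sided (75.98 before rounding). One-sided it is 60. Neither is 57. The inflation step does reproduce: 57 × 1.15 × 1.10 = 72.1, rounded up to 73. The gap between 57 and 76 is a separate sample-size matter; 57 serves here only as the group size at which to compare methods. It is a fair choice: 73 × 0.85 = 62.05 evaluable, and 62.05 / 1.10 = 56.4 after the centre allowance.

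**Power of the t-test at 57 per group.** Standard error = 11.0 × √(2/57) = 2.06, and 5.0 / 2.06 = 2.43. Power from the noncentral t is 67% (68% by the normal approximation).

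**Effect of baseline adjustment on variance.**
- Against a t-test on change: factor (1 + r)/2, below 1 for any r below 1.
- Against a t-test on follow-up scores: factor 1 − r², below 1 for any r above 0.

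**Power with adjustment at 57 per group** (noncentral t, SD = 11.0 × √factor):

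| r | 11.0 is SD of change: factor, SD, power | 11.0 is SD of follow-up score: factor, SD, power |
|---|---|---|
| 0.4 | 0.70, 9.20, 82% | 0.84, 10.08, 75% |
| 0.5 | 0.75, 9.53, 79% | 0.75, 9.53, 79% |
| 0.6 | 0.80, 9.84, 77% | 0.64, 8.80, 85% |
| 0.7 | 0.85, 10.14, 74% | 0.51, 7.86, 92% |

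Each entry compares with 67% for the corresponding unadjusted t-test. The gain is about 7 to 15 percentage points on the change reading and 8 to 25 on the follow-up reading.

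At r = 0.5 the adjusted requirement is 75.98 × 0.75 = 56.98, which matches the stated 57. The article mentions no such assumption, so this cannot be taken as the source of its figure.

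**The case against.** The strongest reply is that the sentence already permits the remedy: linear regression is named and can hold the baseline score. The article condenses a fuller protocol, and covariate lists are commonly left to that document or to the analysis plan. This stands to the extent that the absence of a covariate list is no fault. It does not rescue the t-test, which the article names as an acceptable alternative although it cannot meet the article's own statement on centres.

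Stronger readings are tempting but not supported:

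- **That the t-test throws the baseline away.** The sample size is framed as improvement, so the natural t-test is on change from T0. That uses the baseline, only less efficiently than adjustment.
- **That the method will be chosen after the data are seen, opening the way to selective reporting.** The article says nothing about when the choice is made, and an analysis plan not shown may fix it.
- **That the t-test implies complete cases only.** The article does not describe missing-data handling, and it states intention to treat for the primary analyses.
- **That different methods at T3 and T15 are in themselves an error.** The article separates the two phases deliberately, and long-term PF already goes to mixed models.
- **That time since transplantation is ignored.** Entry is open for up to a year after transplantation, and a stratified analysis by this variable is foreseen. That does not replace adjustment, but adjusting for it is a refinement.

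The power shortfall itself belongs to the sample-size statement. It shows why the lost precision matters here; it is not caused by the choice of test.

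**Conclusion.** The point holds as one of efficiency and internal consistency. The article permits a test for short-term SF-36 PF that cannot include the random centre factor it announces and that is less precise than adjusting for the T0 score it already collects. Randomisation still protects the t-test from systematic bias; what is lost is precision.

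The direction of the gain is secure: adjustment helps for any correlation above 0 against a follow-up-score t-test and for any below 1 against a change-score t-test. The size is less certain. The range of 74% to 92% against 67% depends on a correlation and a type of SD that the article does not give, and on a two-sided test, which it does not state. On the change reading with r = 0.7, adjustment recovers only about half of the gap to 80%, so it should not be presented as a full cure for the sample size.

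**What to change.** For SF-36 PF, delete the t-test option and name one baseline-adjusted model. Either of these would do:

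- linear regression (ANCOVA) at T3 with T0 PF as covariate and a random centre effect, which in practice makes it a mixed model; or
- the mixed model already planned for the long term, extended to give the T3, T6 and T15 contrasts, with T0 PF as covariate and centre as stated.

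Also state whether SD 11.0 refers to the score or to the change, whether the test is two-sided, and what correlation, if any, lies behind the 57. Adding time since transplantation or training setting as covariates is optional.

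The cost is a change of wording and slight extra analysis work. T0 PF is already scheduled, so no new measurement is needed.

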## Abstract

**Background:**

Low physical activity and reduced physical functioning are common after renal transplantation, resulting in a reduced quality of life. Another common post-transplantation complication is poor cardio-metabolic health, which plays a main role in long-term outcomes in renal transplant recipients (RTR). It is increasingly recognized that weight gain in the first year after transplantation, especially an increase in fat mass, is a highly common contributor to cardio-metabolic risk. The aim of this study is to compare the outcomes of usual care to the effects of exercise alone, and exercise combined with dietary counseling, on physical functioning, quality of life and post-transplantation weight gain in RTR.

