### Exercise + diet intervention

The exercise training program in the exercise + diet intervention group is identical to that of the exercise intervention group, and additionally, participants receive dietary counseling. The dietary counseling runs throughout the entire 15 months of the study period and consists of a total of 12 counseling sessions with a renal dietician. The dietary counseling takes place in the hospital face-to-face. If this is not feasible some counseling sessions are done by phone. The dieticians are trained to use motivational interviewing techniques which they apply during the dietary counseling sessions.

Goals are set to improve nutrition status to preserve renal function, to prevent weight gain, type 2 diabetes, and hypercholesterolemia. These goals are set together with the participant to facilitate an autonomy supportive counseling climate [33]. A three-day food diary is used as input during the dietary consultations and for personal goal setting. Participants also receive a food logbook which contains information and exercises to help the participant set diet goals. During the dietary counseling sessions, special attention is given to salt intake, whole-wheat grains and fruit and vegetable intake, intake of saturated and unsaturated fat, and the use of sugar-rich products, sugar-sweetened beverages (soft drinks, sweetened dairy drinks and fruit juices) and preventing overeating. In addition, participants are reminded of their physical activity goals, and the importance of protein intake for maintaining and increasing muscle mass. In case of disease after transplantation, for example infections, the dietician assists the patient in maintaining an energy- and protein-rich diet to prevent further deterioration or decline in muscle mass.

Dietary counseling session 9 (of total 12) is a group meeting for which the participants are encouraged to bring significant others such as their partner or other supportive family members. The dietary counseling is in line with the 2006 Guidelines for a Healthy Diet by the Dutch Food and Nutrition Council [34], supplemented with diet guidelines for RTR [35] and diet guidelines for the prevention of type 2 diabetes [36] and cardiovascular risk [37].

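### The short-term contrast on SF-36 PF is not named: the sample size fits both exercise arms pooled against usual care, while the aims point to separate comparisons that would have about 67–71% power, not 80%

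*Protocol article*

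**What the plan says.** Protocol article, Statistical analyses: "Short term differences between groups will be tested using students T-test or linear regression". Long-term differences go to mixed models. No contrast among the three arms is named for either.

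Text that fits a pooled exercise contrast in the short term:
- Screening, recruitment and randomization plans an "expected improvement on the physical functioning scale of quality of life of 13.8 points in the intervention group and 8.8 points in usual care", with "α=0.05, β= 0.80, SD = 11.0". It concludes: "This results in a required number of 57 RTR per group". Only one intervention group appears.
- Exercise + diet intervention: "The exercise training program in the exercise + diet intervention group is identical to that of the exercise intervention group".
- Outcomes: "Effectiveness of the diet intervention will be determined at 15 months".

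Text that fits separate contrasts:
- The abstract's aim is to "compare the outcomes of usual care to the effects of exercise alone, and exercise combined with dietary counseling". The trial description in Methods/design and the aim in the Discussion also present two distinct interventions.
- Health economic analysis compares each intervention with usual care.

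**The concern.** A two-sample t-test in a three-arm trial requires a choice of which groups to compare. Here the choice decides whether the trial has the power it states. The sample-size figure and the aims imply different contrasts, and the analysis text does not settle between them.

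If separate comparisons are used, the trial is smaller than its own 80% requires. Two noisy estimates of largely the same training effect may also disagree by chance. In a simulation with a true effect of 5.0 in both arms and 62 completers each, exactly one of the two pairwise tests was significant in about 28% of trials. If the pooled contrast is used, the stated power holds approximately, but the result does not answer the aims as worded. Leaving the choice open also lets it be made after the data are seen.

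**Working it through.** **Inputs** (Screening, recruitment and randomization): difference 13.8 − 8.8 = 5.0 points; SD 11.0; α 0.05; 57 evaluable and 73 randomised per group; 15% dropout; 10% centre correction. Assumptions: a two-sided test, and the printed β of 0.80 meaning power 0.80. Short term is taken as T3, the end of the 3-month training phase.

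**Reproducing 57.** With (1.960 + 0.842)² = 7.849 and SD²/difference² = 121/25 = 4.84:
- 2:1 pooled, usual-care n = (1 + 1/2) × 7.849 × 4.84 = 56.98, so 57 (against 114 exercisers).
- 1:1, n per group = 2 × 7.849 × 4.84 = 75.98, so 76.
- One-sided variants give 60 (1:1) and 45 (2:1).

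Of these variants only the two-sided 2:1 contrast gives 57. The inflation is also consistent: 57 × 1.15 × 1.10 = 72.1, rounded up to 73.

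**Power for a 5.0-point difference.** The standard error (SE) is 11 × √(2/n) for one arm against usual care, and 11 × √(1/n + 1/(2n)) for both arms against usual care. Completers per arm: 73 × 0.85 = 62. With the centre correction, effective n = 62/1.1 = 56.4.

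| n per arm | One arm v usual care: SE | Power, normal (t) | Both arms v usual care: SE | Power, normal (t) |
|---|---|---|---|---|
| 57 | 2.06 | 68.0% (67.2%) | 1.78 | 80.0% (79.6%) |
| 62 | 1.98 | 71.6% (70.9%) | 1.71 | 83.2% (82.8%) |
| 56.4 | 2.07 | 67.5% (66.7%) | 1.79 | 79.6% (79.1%) |

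With no dropout at all (73 per arm) the pairwise power is 78.4% by the normal formula, still short of 80%.

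**Sensitivity to a smaller exercise + diet effect at T3.** With exercise alone at 5.0 and exercise + diet at 4.0, pooled power at 62 per arm is 74.4%. Pooled and exercise-only power break even at a pooled mean of about 5 × 1.711/1.976 = 4.33, that is, an exercise + diet effect of 2 × 4.33 − 5 = 3.66.

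**Cost of gating.** If the exercise-only claim must pass both the pooled test and its own test, simulation at 62 per arm gives power of about 69% when both effects are 5.0, against 71% ungated. It is about 66% if exercise + diet is 4.0 and about 60% if it is 3.0.

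**The case against.** **The contrast belongs in an analysis plan.** The article condenses a fuller protocol, and silence on a contrast is not in itself a defect. That stands. What remains is that a figure the article does state (57) and aims it does state imply different contrasts, and the 80% is true of only one of them.

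**The plan already pools.** The single intervention group, the exact match of 57 and the diet effect being judged at 15 months all fit a pooled short-term test. This is fair, and it rules out a stronger reading that a reader might infer: that the plan sets each arm separately against usual care at T3, uses only half the exercisers in each test and never produces the pooled estimate. The analysis section says no such thing. Separate testing is an inference from the aims. Equally, no sentence says that the arms will be pooled, so the opposite reading is not established either.

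**The two arms are not the same treatment at T3.** Dietary counselling runs through the whole 15 months and includes reminders about activity goals and protein intake. The Background ties the response to exercise to nutritional status. An early difference between the arms is therefore possible, and keeping them separate would be a legitimate choice for a pragmatic trial. This stands as a limit on what the pooled estimate means.

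**Pooling first does not help the separate claims.** Correct: the gate lowers power for the exercise-only claim. The gain is one adequately powered answer about training and control of the error rate across the two follow-on tests.

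**Conclusion.** The point holds in limited form. The short-term contrast on the primary outcome is unnamed, and the document is inconsistent about it: the sample size corresponds to a pooled 2:1 comparison, the aims to separate ones. If the analysis is separate, power is about 67–68% at the stated 57 and about 71% at 62 completers, or about 67% after the centre correction. The pooled contrast gives about 80%, 83% and 79%.

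This rests on a two-sided 5% test, on β being meant as power, on T3 as the short-term time point, and on a 5.0-point effect in both exercise arms. That 57 matches the pooled formula shows which calculation reproduces it, not what the authors intended.

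**What to change.** In Statistical analyses, state that the first test of SF-36 PF at T3 is the mean of the exercise and exercise + diet arms minus usual care, estimated from one three-arm model. If it is significant, test each arm against usual care at 5%. The pooled contrast is then the intersection test of a closed procedure, so α is not split. Keep the arms separate at T15, where the diet effect is judged.

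In the sample-size paragraph, state that the 80% applies to the pooled contrast and that each pairwise comparison has about 67–71%. Give the sidedness and correct the power notation.

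State two downsides. The pooled estimate is the effect of training with or without diet, because counselling starts before T3. And the gate lowers exercise-only power from about 71% to 69%, or to about 66% or 60% if the exercise + diet effect is 4.0 or 3.0.

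The cost is one paragraph of analysis text and a sentence or two on sample size. No new data or participants are needed. The alternative, keeping separate primary comparisons at 80%, would need 76 evaluable per group before any inflation for dropout and centres.
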